#### Data management

In the study, data will be entered electronically in an Excel file. Participant files will be stored in numerical order and stored in a secure and accessible place and manner. Participant files will be maintained in storage for a period of 3 years and uploaded to a web-based public database (ResMan research manager http://www.medresman.org.cn/pub/cn/proj/guide.aspx) upon completion of the study. The option to choose a value from a list of valid codes and a description of what each code means will be available where applicable.

### Statistical analysis

Statistical analysis will be completed using SPSS (version 24.0). In order to compare the difference at baseline between the two groups, the two-sample t-test will be used for continuous variables and the χ^2^ test for classified data. Analyses of differences between two groups regarding maternal and neonatal morbidity outcomes, IIFAS, BKQ, BSES-SF, PAQ, PSAS-CN, EPDS and SSRS are evaluated in the same manner. In addition, one-way ANOVA analysis and two-sample t-test will be used to explore the influencing factors of the EBF rate. The data from the IIFAS, BKQ, BSES-SF, PAQ, PSAS-CN, EPDS and SSRS of the two groups at different time points (T0, T1, T2 and T3) will be tested using repeated measurement Analysis of Variance (ANOVA). For variables that have an interaction effect in repeated measurement ANOVA, a simple effect analysis will be carried out to further explore the effects of each factor. Cohen’s d will be reported to check the effect size. Cohen’s d will be used to evaluate the magnitude of difference between the two groups. According to the standard established by Cohen, the large, medium and small of the effect of d was divided into 0.8, 0.5, and 0.2 [48]. The randomized trial will use the statistical analysis “per protocol”. The significance level is set to less than 0.05 (double-tailed). P-values will be reported to four decimal places p-values and those less than 0.001 will be reported as p < 0.001.

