### Sample size

The current EBF rate for infants under 6 months of age in China is 34.1% [3]. After the intervention, the rate is expected to increase to 60%, which was required by the *National Nutrition Plan (2017–2030)* [5]. Sample size was calculated for EBR in 6 months for a two-sided hypothesis test with a power of 90% and a significance level of 0.05. Therefore, according to the following formula, the study requires a minimum sample size of 76 (each group). Considering a 20% lost follow-up rate and 20% withdrawal rate because of failure to participate in the full intervention due to prematurity, a total of 218 participants will be needed for the study.$${n}_{1}={n}_{2}=\frac{{{[u}_{\alpha }\sqrt{2P\left(1-P\right)}+{u}_{\beta }\sqrt{{P}_{1}\left({1-P}_{1}\right)+{P}_{2}\left({1-P}_{2}\right)} ]}^{2}}{{(P1-P2)}^{2}}$$

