### Randomization

All patients who consent to participate and who fulfill the inclusion criteria will be randomized. Eligible participants will be randomly assigned to the IG and the CG based on a table of random numbers (https://www.sealedenvelope.com/). Results of random allocation will be placed in an opaque envelope.

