### Data collection

#### Basic information questionnaire

A researcher-designed questionnaire of socio-demographic information will be used to collect basic information about participants, including gestational age, number of pregnancies, parity, education level, family monthly income, employment status, length of maternity leave, co-parenting members, conception mode at baseline; and delivery mode, weeks of delivery, time of breastfeeding initiation, separation of mother and infant, and presence of comorbidities at 1 month postpartum.

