The methodological strength of this study is that literature review and qualitative interviews were used during the intervention design of this study to synthesize the experience of previous studies and the actual needs of pregnant women to better support them. This intervention program went through two rounds of expert consensus based on the Delphi method [25], and a total of 12 experts from one university and seven hospitals completed the questionnaire based on the experts’ consensus to assess the importance and rationality of this intervention program. The strengths of the intervention are the addition of appropriate sessions based on the actual needs of the participants and the provision of individualized counseling and guidance. Blixt et al. [64] highlighted the importance of professionals providing evidence-based breastfeeding support in an individualized manner, which may enhance the positive nature of women’s breastfeeding experience.

However, this study will be conducted in only one baby-friendly hospital in a large city in central China, and a multicenter trial cannot be conducted. This might influence the generalizability of the research findings to other regions. Furthermore, due to the social desirability, women who are interested in or willing to breastfeed will participate well in this study, which may result in some biases.

Considering the large disparity in EBF rates between China and the WHO’ recommendations, such a study is needed in order to provide pregnant women with reliable breastfeeding support from the policy system, family, hospital, community and individual levels and provide a reference for countries around the world. This study synthesizes resources at all stages of a woman’s breastfeeding journey to support breastfeeding promotion and provides a new perspective for adding breastfeeding interventions to prenatal and postnatal care for hospital and community healthcare providers.

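### Baseline differences between randomised arms are to be significance-tested, while no collected baseline predictor is named for the 6-month exclusive breastfeeding comparison, at some cost in precision

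*Protocol article*

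**What the plan says.** Under Statistical analysis, the protocol article sets out the baseline comparison as follows: "In order to compare the difference at baseline between the two groups, the two-sample t-test will be used for continuous variables", and a chi-square test for categorical variables. The same tests are then applied to morbidity and to the seven scales. EBF is not in that list. It appears in this section only where its possible determinants are to be explored by one-way ANOVA and t-test. The chi-square test is the only test named for categorical data, and it is unadjusted.

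The Basic information questionnaire collects, at baseline, items "including gestational age, number of pregnancies, parity, education level, family monthly income, employment status, length of maternity leave", together with co-parenting members and mode of conception. The infant feeding attitude scale (IIFAS) and the other scales are listed from T0 and enter a repeated-measures ANOVA. The Blinding section places baseline collection before the envelopes are opened.

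The sample size rests on EBF within 6 months: "The current EBF rate for infants under 6 months of age in China is 34.1"%, and "the rate is expected to increase to 60"%, "for a two-sided hypothesis test" "with a power of 90% and a significance level of 0.05".

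**The concern.** Baseline values are measured before allocation is revealed. For the whole randomised set, the null hypothesis of a baseline test is therefore already known to be true. A small p-value shows only that chance has acted. A large one does not show that an imbalance is harmless to the EBF result, because that depends on how strongly the variable predicts EBF, and the test does not measure this.

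The useful role for these variables is as covariates in the EBF comparison. There they narrow the confidence interval and correct for whatever imbalance the one realised randomisation produced. The article expects some factors to influence EBF but keeps them in a univariate exploration, apart from the comparison of arms. At stake is the width of the interval for the 6-month EBF difference, not its validity.

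**Working it through.** **Inputs from the article.** EBF 34.1% versus 60%, two-sided alpha 0.05, power 90%, 76 per arm before losses, 109 per arm randomised. Prognostic strength of the covariates, the share of parous women and the effect of parity on EBF are not given, so they are assumed below and varied where possible.

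**1. The plan's own figure.** With P = (0.341 + 0.60)/2 = 0.4705:

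- 1.960 × √(2 × 0.4705 × 0.5295) = 1.383
- 1.282 × √(0.341 × 0.659 + 0.60 × 0.40) = 0.874
- n = (1.383 + 0.874)² / 0.259² = 75.95, so 76 per arm, as stated.
- 76 × 1.2 × 1.2 = 109.4, so 109 per arm and 218 in total, as stated.

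**2. What the baseline tests would return.** Nine questionnaire items are collected at baseline, and six of the seven scales could sensibly be given in pregnancy (the schedule figure is not shown). If the tests were independent, the chance of at least one p < 0.05 under perfect randomisation is 1 − 0.95⁹ = 37% for the nine items and 1 − 0.95¹⁵ = 54% for all fifteen.

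**3. Size of a chance imbalance.** Assume 50% parous and simple 1:1 randomisation.

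- At 109 per arm the SD of the difference in proportion parous is √(2 × 0.25/109) = 6.8 points, and the 95% limit is 1.96 × 6.8 = 13.3 points. An imbalance of 10 points or more has probability 14%.
- If parity shifts EBF by 10, 20 or 30 points (assumed), an imbalance at that limit moves the observed EBF difference by 1.3, 2.7 or 4.0 points.
- At 76 per arm the limit is 15.9 points, an imbalance of 10 points or more has probability 22%, and the shift at 20 points is 3.2.
- For scale, the planned difference is 25.9 points. The 95% CI half-width at 109 per arm is 1.96 × √(0.4647/109) = 12.8 points, where 0.4647 = 0.341 × 0.659 + 0.60 × 0.40.

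**4. Precision gained by adjustment.** The simulation used one standard-normal baseline score, with marginal EBF rates held at 34.1% and 60% and 2,000 trials per row. Variance compares the standardised risk difference from a logistic model (arm plus score) with the raw difference. Power compares the Wald test for arm in that model with the pooled two-proportion test.

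| Per arm | Assumed log-odds ratio per SD | Variance, adjusted / unadjusted | Power, unadjusted | Power, adjusted |
|---|---|---|---|---|
| 76 | 0.3 | 1.00 | 89.2% | 89.9% |
| 76 | 0.5 | 0.94 | 90.0% | 91.7% |
| 76 | 0.8 | 0.88 | 89.2% | 93.2% |
| 76 | 1.2 | 0.78 | 89.1% | 95.9% |
| 109 | 0.8 | 0.89 | 97.3% | 98.6% |

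Part of the power gain comes from the choice of comparator. At 76 per arm the unpooled standard error is √(0.4647/76) = 0.0782, and 0.259/0.0782 − 1.96 = 1.35, which gives 91.2% power against 90.0% for the pooled test. The 0.7-point gain in the first row, where variance does not change, should not be read as a precision gain.

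**5. Validity.** At 76 per arm the mean unadjusted difference was 0.256 to 0.261 against a true 0.259. Under the null (3,000 trials, log-odds ratio 0.8) rejection was 5.6% unadjusted and 5.3% adjusted. With a Monte Carlo standard error of √(0.05 × 0.95/3000) = 0.4 points, both are compatible with 5%.

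**The case against.** The best defence is that this is mostly silence. A condensed article commonly leaves covariates to a fuller protocol or analysis plan, and the unadjusted comparison is sound in any case. Much of that stands. Four stronger readings are tempting, and the document does not support them.

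- *The plan fixes an unadjusted primary test.* It names no between-arm test for EBF. The chi-square test is given for baseline and secondary comparisons.
- *Comparability, or the choice of analysis, will be decided by the baseline p-values.* The text says only that differences will be compared and attaches no decision to the result. Nor is baseline information unused elsewhere, since T0 scores enter the repeated-measures ANOVA.
- *Chance imbalance biases the EBF result.* Over repeated randomisation it does not, and the standard error already allows for it. Any shift in a given trial is in proportion to prognostic strength, and even at the limits in step 3 it is well inside the CI half-width.
- *The design makes imbalance likely.* Allocation is "based on a table of random numbers", which is silent on stratification but does not exclude it. The Discussion's remark that "women who are interested in or willing to breastfeed will participate well in this study" concerns who volunteers. That affects both arms and generalisability, not balance between them.

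The document does not rank predictors either. The reliability it reports for the Chinese IIFAS (0.589 to 0.685) is modest, so a strong covariate effect cannot be presumed. The stated per-protocol analysis can create differences that are not due to chance, but that is a separate matter and lends no weight here.

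What the defence does not reach is the explicit instruction to test baseline differences, and the near absence of cost in using data already collected.

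**Conclusion.** The point holds as one of efficiency. The baseline tests are prescribed and uninformative, and no collected baseline variable is named for the EBF comparison. Adjustment would reduce the variance of the risk difference by 0 to 22% over the assumed strengths (log-odds ratio 0.3 to 1.2 per SD of one score). That is worth roughly 1 to 7 points of power at 76 per arm, part of it due to the comparator, and about 1 point at 109 per arm for the one strength tried. If the covariates are weak, the gain is near nil. Nothing here shows bias or an inflated type I error. The change is worth making because it costs little, not because the trial would otherwise mislead.

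**What to change.** 1. Replace the baseline significance tests with a descriptive table by arm, without p-values.
2. Pre-specify the 6-month EBF comparison as a logistic model with arm and a short fixed list of covariates: parity, a category combining employment and maternity leave, baseline IIFAS, and the baseline breastfeeding self-efficacy score if it is in fact measured at T0.
3. Report the standardised (marginal) risk difference with its 95% CI, and the unadjusted difference alongside.

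The cost is a change of wording in the analysis section. The questionnaire covariates and IIFAS are already collected, so no new data are needed. The primary model becomes slightly more complex, and the marginal risk difference with its interval takes a calculation beyond the fitted coefficients. The quantity estimated remains a difference in EBF rates.

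### The secondary scales are analysed by t-tests that ignore baseline and by a repeated-measures ANOVA that counts baseline as an outcome and, in its classical form, drops any woman who misses a visit

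*Protocol article*

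**What the plan says.** The Statistical analysis section of the protocol article names two methods for the scales. The first is the method used for the baseline comparison: "the two-sample t-test will be used for continuous variables", and the outcomes "IIFAS, BKQ, BSES-SF, PAQ, PSAS-CN, EPDS and SSRS are evaluated in the same manner". No covariate is named. The second is longitudinal: the scores of all seven scales at T0, T1, T2 and T3 "will be tested using repeated measurement Analysis of Variance (ANOVA". It is followed up as "For variables that have an interaction effect in repeated measurement ANOVA, a simple effect analysis will be carried out".

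The same section fixes the software ("Statistical analysis will be completed using SPSS (version 24.0") and the analysis population ("The randomized trial will use the statistical analysis “per protocol").

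The Sample size section sets the expected attrition: "Considering a 20% lost follow-up rate and 20% withdrawal rate", the withdrawal being attributed to prematurity that prevents full participation. Visits are at baseline (28 to 35 weeks of gestation) and at 1, 4 and 6 months postpartum.

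**The concern.** Three features of the named methods fit this trial poorly.

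- **Baseline is ignored in the t-tests.** A score taken before randomisation usually predicts the later score on the same scale. Leaving it out gives up precision that costs nothing.
- **Baseline is an outcome level in the ANOVA.** The intervention cannot change T0. Averaging T0 with the three follow-up visits dilutes the group main effect and moves the treatment effect into the group-by-time interaction.
- **Classical repeated-measures ANOVA needs complete profiles.** One missed visit removes the woman and the scores she did give. The plan anticipates substantial loss, and depression, self-efficacy and feeding attitude may well be related to who stays in a breastfeeding study.

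The list of scales is a further problem. PAQ, described as built for pregnant women and covering worry about the fetus and childbirth, and PSAS-CN, a postpartum scale, are both entered in the T0 to T3 model. From those descriptions, neither is likely to have four comparable time points.

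Attitude, knowledge and self-efficacy are named in the trial's aim, so the precision and validity of these comparisons matter even though they are secondary.

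**Working it through.** **Plan's own figures.** With 34.1% versus 60%, two-sided 0.05, 90% power and the pooled formula in the Sample size section: [1.960 × √(2 × 0.4705 × 0.5295) + 1.282 × √(0.341 × 0.659 + 0.60 × 0.40)]² / 0.259² = 75.9, so 76 per group, as stated. Then 76 × 1.2 × 1.2 = 109.4, which gives 109 per arm and 218 in total. These figures concern the exclusive breastfeeding rate. No sample size is given for the scales.

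**Planned loss.** 20% alone leaves 80%. Applying both 20% figures in turn leaves 0.8 × 0.8 = 64%, a loss of 36%.

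**Women with a follow-up score that complete-profile ANOVA discards.** The article does not give the timing of dropout. I assume that the same proportion of remaining women is lost at each of the three visits and that nobody returns.

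- 20% loss: retention per visit is 0.80^(1/3) = 0.928, so 93% are seen at T1, 86% at T2 and 80% at T3. Seen at T1 but not complete: (0.928 − 0.80) × 218 = 28 women.
- 36% loss: retention per visit is 0.64^(1/3) = 0.862, so 86% are seen at T1, 74% at T2 and 64% at T3. Seen at T1 but not complete: (0.862 − 0.64) × 218 = 48 women.

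**Precision.** Let r be the correlation between two visits. It is not in the article; 0.3 to 0.7 is assumed. The last column also assumes equal correlation between all visits and an equal effect at T1 to T3, so that including T0 shrinks the group main effect to 0.75 of its size.

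| r | SE, adjusted vs t-test: √(1 − r²) | N, t-test vs adjusted: 1/(1 − r²) | N, change from T0 vs adjusted: 2/(1 + r) | N, ANOVA group main effect vs adjusted follow-up mean: [(1 + 3r)/4 ÷ 0.75²] ÷ [(1 + 2r)/3 − r²] |
|---|---|---|---|---|
| 0.3 | 0.954 | 1.10 | 1.54 | 1.90 |
| 0.5 | 0.866 | 1.33 | 1.33 | 2.67 |
| 0.7 | 0.714 | 1.96 | 1.18 | 4.44 |

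The fourth column is the fairest single-visit comparison with the group-by-time analysis, because a T3-versus-T0 contrast between groups is a comparison of changes.

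In terms of power at an assumed standardised difference of 0.4:

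- 87 per arm (109 × 0.8): 75% unadjusted, against 79%, 86% or 96% adjusted at r = 0.3, 0.5 or 0.7.
- 69 per arm (109 × 0.64 = 69.8): 65% unadjusted, against 69%, 77% or 91% adjusted.

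**Bias, by simulation.** When dropout is unrelated to the scores, both the complete-profile T3 difference and a baseline-adjusted estimate from all available scores recover a true 0.40 (to within 0.01). In a deliberately strong case, where dropout depends on the previous score in the control arm only, the complete-profile difference averages 0.32, 0.28 or 0.23 (r = 0.3, 0.5, 0.7) at 20% nominal loss, and 0.27, 0.20 or 0.12 at 36%. The all-data estimate stays at about 0.40. This shows that bias can arise; it does not predict its size here.

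**The case against.** Repeated-measures ANOVA followed by simple effects is a recognised analysis of secondary outcomes, and several stronger readings of this point go too far.

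- **A reader might infer that the baseline scores are wasted.** They are not. T0 is one of the four ANOVA levels and enters through group-by-time. It is used inefficiently, and it is ignored only in the t-tests.
- **A reader might infer that the whole plan discards partial data.** A t-test at one visit uses every woman scored at that visit, so the loss of partial profiles is confined to the ANOVA.
- **A reader might take every anticipated loss as discarded data:** 0.20 × 218 = 44 women, or 78 to 87 at 36% to 40%. Those counts include women lost before T1, who have no follow-up score for any model to use. They also include withdrawn women whom the per-protocol rule could remove whatever the model.
- **A reader might conclude that the results will be biased.** That depends on the dropout mechanism. A mixed model protects only under missing at random; if dropout follows current, unrecorded depression, it too can be biased.

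It can also be said that the article never states listwise deletion, and that missing-data handling may sit in an analysis plan that is not shown. That stands: deletion is inferred from the classical form of the named procedure. The choice of unadjusted t-tests and of an ANOVA with T0 as an outcome is stated in the article, and that part of the point needs no inference.

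**Conclusion.** The point holds as a matter of efficiency and possible bias in the secondary outcomes. The article commits to comparisons that ignore baseline or treat it as an outcome, and to a longitudinal method that sits badly with the attrition it plans for.

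The size is about 28 to 48 of 218 women with a follow-up score lost to the ANOVA, given dropout spread evenly over the visits and classical complete-profile handling. The upper figure also assumes that the withdrawn women drop out in the same pattern and are not already excluded as protocol deviators. Against the t-test, baseline adjustment would make standard errors 5% to 29% smaller at the assumed correlations. The direction and size of any bias cannot be derived from the article.

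The sample size and test of the breastfeeding rate are untouched. The change is well worth making, but its absence does not invalidate the trial.

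**What to change.** For IIFAS, BKQ, BSES-SF, EPDS and SSRS, replace the t-tests and the ANOVA with one linear mixed model per scale:

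- outcomes: the scores at T1, T2 and T3;
- population: all randomised women with at least one follow-up score. This departs from the per-protocol rule and must be stated, since a mixed model alone does not bring back women whom that rule removes;
- fixed effects: group, visit and group-by-visit, with the baseline score as covariate;
- covariance: unstructured across visits;
- report: the adjusted group difference at 6 months with its 95% confidence interval.

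For PSAS-CN, use the same model on T1 to T3 without a same-scale baseline covariate; baseline PAQ may serve as covariate instead. Remove PAQ from the postpartum longitudinal analysis, because it measures pregnancy-related anxiety.

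The cost is slightly more analysis work and output less familiar than an ANOVA table. No new data are needed, and SPSS 24 has a mixed-model procedure. The model relies on missing at random, which should be stated as an assumption.

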### Blinding

Allocation details will be placed in opaque and sealed envelopes by a study coordinator and concealed from recruiters, data collectors and the group allocator. After recruitment and baseline data collection, the other study coordinator will open the envelopes and allocated participants. Due to the nature of the intervention, intervention conductors and participants will not be blinded to group allocation. The data collector will be masked to group allocation during data collection and the statistician will also be masked during data analyses.

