### Interventions

#### Control group

Participants in the CG will receive usual prenatal and postnatal care. At the same time, they will be contacted by the researchers upon initial enrollment in the study but receive no further guidance and interventions.

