Skill Session 2	1. how do I use a breast pump? 2. How do I store and warm breastmilk? 3. How do I breastfeed after work? 4. How do I wean properly? 5. Additional feeding knowledge of interest to pregnant mothers.

1. Format: online Tencent meeting; duration: 1 h per theory session and 40 min per skill session

2. The four sessions will be completed before the delivery, and the specific time of each class will be adjusted according to the availability of the participants and their families

3. Participants can invite at least one family member to attend each lecture

4.Lectures will be offered in small groups of five to ten participants per session

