#### Participant withdrawal

Participants may withdraw from the study for any reason at any time. The investigator may also eliminate participants from the study in order to protect their safety and/or if they are unwilling or unable to comply with required study procedures after consultation with the researchers.

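### Per protocol, left undefined, is the only analysis of this superiority trial, although the plan expects sizeable removals after randomisation that may be unequal between arms

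*Protocol article*

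**What the plan says.** In the protocol article:

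- **Statistical analysis** fixes the analysis set: "The randomized trial will use the statistical analysis “per protocol". The term is not defined, and no set of all randomised women appears anywhere in the article.
- **Sample size** makes two allowances: "Considering a 20% lost follow-up rate and 20% withdrawal rate because of failure to participate in the full intervention due to prematurity".
- **Control group** gives these women usual care and a contact at enrolment, after which they "receive no further guidance and interventions".
- **Intervention group**, notes to Table 2, says of the prenatal lectures: "The four sessions will be completed before the delivery". Table 1 continues the programme to one month postpartum.
- **Participant withdrawal** lets the investigator remove participants "if they are unwilling or unable to comply with required study procedures after consultation with the researchers". No arm is named.
- **Blinding** places allocation before all of these events: "After recruitment and baseline data collection, the other study coordinator will open the envelopes". Women enter at 28 to 35 weeks of gestation.

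**The concern.** The trial tests superiority over usual care. In such a trial, the protection against confounding comes from comparing the groups as randomised. Here the stated analysis compares whoever remains after exclusions that depend on what happened later: early delivery, incomplete attendance or non-compliance.

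Two features make this more than a formality. First, these events plausibly relate to the outcome. Preterm delivery and poor engagement could both go with less exclusive breastfeeding, and the article's Discussion itself expects women interested in breastfeeding to take part well. Second, control women have no study programme to complete. Read literally, the largest planned exclusion therefore cannot apply to them. If removal is unequal and the removed women have lower EBF, the intervention arm's rate rises without any effect of the intervention, and the 5% significance level no longer holds.

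**Working it through.** **Inputs from the protocol article.** Control EBF 34.1%; intervention EBF 60%; two-sided alpha 0.05; power 90%; 76 per group before allowances; 109 per group randomised; 20% loss to follow-up; 20% withdrawal.

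**Assumptions, not in the article.** The EBF rate q among removed women, and the share of each arm removed.

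**1. The plan's own figures.** The printed formula, with P = (0.341 + 0.60)/2 = 0.4705, gives 75.95, so 76 per group. Then 76 × 1.2 × 1.2 = 109.4, so 109 per group and 218 in total. Both stated figures reproduce. The withdrawal allowance was applied equally to both arms.

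**2. Numbers analysed.** After 20% loss, 109 × 0.8 = 87.2, about 87 per arm. After a further 20%, 109 × 0.8 × 0.8 = 69.8, about 70. If the second removal falls only on the intervention arm, the comparison is 70 intervention women against 87 controls.

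**3. Shift under no true effect.** With true EBF of 34.1% in both arms, the rate among retained intervention women is (0.341 − 0.2q)/0.8. The two-sided rejection probability uses the pooled two-proportion z-test (normal approximation), where d is the spurious difference:

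Φ[(d − 1.96·SE₀)/SE₁] + Φ[(−d − 1.96·SE₀)/SE₁]

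SE₀ uses the pooled rate and SE₁ the two separate rates. For q = 10%: retained rate 0.4012, d = 0.0602, pooled rate (70 × 0.4012 + 87 × 0.341)/157 = 0.3679, SE₀ = 0.0774, SE₁ = 0.0776. The result is Φ(−1.18) + Φ(−2.73) ≈ 0.122.

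| EBF among removed | Retained intervention rate | Spurious gain (points) | Type I error |
|---|---|---|---|
| 34.1% | 34.1% | 0 | 5.0% |
| 20% | 37.6% | 3.5 | 7.5% |
| 10% | 40.1% | 6.0 | 12.2% |
| 0% | 42.6% | 8.5 | 19.5% |

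**4. Fewer removed.** With 10% of the intervention arm removed (87 × 0.9 ≈ 78 against 87), the retained rate is (0.341 − 0.1q)/0.9, or 35.7%, 36.8% and 37.9% for q = 20%, 10% and 0%. The same formula gives type I errors of about 5.5%, 6.5% and 8%.

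**5. Symmetric removal.** If both arms lose the same share with the same EBF among those removed (70 against 70, equal rates), the type I error stays at about 5%.

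**6. Cost of analysing everyone.** If the 20% who do not complete have the control rate, intervention EBF is 0.8 × 0.60 + 0.2 × 0.341 = 0.548. Power against 34.1% is about 79% with 87 per arm and about 87% if all 109 per arm are followed. The fair comparator is the per-protocol comparison of 70 against 87 at 60% v 34.1%, which has about 91%.

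**The case against.** The strongest reply concerns symmetry. A reader might infer that the 20% withdrawal can only happen in the intervention arm and that a control mother who delivers early stays in. The article does not establish this. The stated cause is prematurity, which occurs in both arms; the allowance inflates both arms equally; and the compliance clause names no arm, while controls also have study procedures, namely the questionnaires. The sponsor may have meant to withdraw preterm deliveries from both groups. Against that, the reason given is "20% withdrawal rate because of failure to participate in the full intervention due to prematurity", which does not fit a woman with no intervention to attend, and no rule for preterm controls is written. The text is ambiguous. Even a symmetric exclusion would select on an event after randomisation.

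A second reply is that the 20% is an allowance, not an exclusion rule. Table 1 places the lectures in the first two weeks after recruitment, so many women who deliver preterm could already have finished them. This stands: since per protocol is undefined, the share removed is unknown and may be well below 20%.

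Third, the size of any bias depends on an EBF rate nobody knows. This also stands. If removed women do as well as the rest, there is no bias, and 19.5% requires that none of them breastfeed exclusively.

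The unseen analysis plan does not answer the point. The article does not leave the analysis set open; it states one.

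**Conclusion.** The concern holds in this form: the article commits a superiority trial to an undefined per-protocol analysis alone, while foreseeing removals after randomisation that are plausibly related to exclusive breastfeeding and may be unequal between arms. The allocation procedure is not at fault; it is the analysed groups that would differ from those randomised.

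Bias is possible, not certain. It would favour the intervention under two conditions: unequal removal, and lower EBF among those removed. In the illustrated one-sided case with 20% removed, it runs from nothing to 8.5 points, with type I error from 5% to about 19.5%. A stronger conclusion, that the analysis will necessarily favour the intervention, goes beyond what the article supports. The sentence still needs changing before analysis, because it governs the primary comparison and the remedy is cheap.

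**What to change.** Replace the per-protocol sentence with wording such as: *The primary analysis will include all randomised women in the group to which they were allocated, regardless of prematurity, attendance or compliance. A per-protocol analysis, with its exclusion rule defined in advance and applied identically in both arms, will be supportive only.*

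In Participant withdrawal, separate leaving the intervention from leaving follow-up: feeding data at 1, 4 and 6 months continue to be collected from women who stop the intervention or deliver preterm, unless they withdraw consent to follow-up. In Sample size, state whether the prematurity allowance concerns one arm or both. The method for missing 6-month feeding status can be left to the analysis plan.

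The cost is a change of wording and continued questionnaires for women who do not complete. Follow-up cannot be recovered later, so it must continue while the trial runs. The estimate may be smaller: if the 20% behave like controls, the intervention rate is 54.8% rather than 60%. Power is then about 79% with 87 per arm, or about 87% with complete follow-up, against about 91% for the per-protocol comparison.
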